### Outcomes

The primary outcome is infant pain expression measured with Premature Infant Pain Profile Revised (PIPP-R) [50], which is a pain assessment instrument that has also been translated into Swedish [51].

Secondary outcomes in the RCT are: a) changes in galvanic skin response (GSR) (area small peaks, area huge peaks, peaks per second, average rise time, average peak), which is obtained via three electrodes on the infant’s foot [52], b) parents’ rating of the infant’s pain, c) parents’ rating of their own stress during the procedure and d) parents’ rating of how beneficial the pain management they were involved in felt to them and their infant.

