### Eligibility criteria

Healthy newborn infants, who will be screened with the routine newborn metabolic screening test and their parent are enrolled. Infants treated with sedatives or analgesics within the last 24 h are excluded. A written informed consent is acquired from the infant’s parents. Parents who understand Swedish or English are eligible for inclusion. The infant-parent dyad is randomly assigned to one of three treatment groups; one standard of care group with glucose (*n* = 75), one group with skin-to-skin contact (n = 75), and one group where skin-to-skin contact is combined with breastfeeding (if applicable) and live parental lullaby singing (n = 75), (Table 1).

**Table 1 Tab1:** Treatment groups

Group	Treatment	Treatment description
Group 1	Standard care with glucose	The infant is placed on the examination table for the blood test. Standard care comprises facilitated tucking done by a nurse or the parent, 1–2 ml of oral glucose (300 mg/ml) given in fractioned doses from 2 min before the procedure and the opportunity to suck on a pacifier or on a parent’s or a nurse’s plastic gloved finger.
Group 2a	Parent-driven pain management with skin-to-skin contact	The parent will sit in an adjustable recliner chair during the procedure and the infant will be placed naked (except for a diaper and possibly a hat) on the parent’s bare chest 10 min before the venipuncture. The skin-to-skin contact will proceed during and a while after the procedure.
Group 2b	Parent-driven pain management with skin-to-skin contact and breastfeeding	The parent will sit in an adjustable recliner chair during the procedure and the infant will be placed naked (except for a diaper and possibly a hat) on the parent’s bare chest 10 min before the venipuncture. Breastfeeding starts about 2 min before the venipuncture and the blood test is performed when the infant is latched and sucking well.

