### Study measures

The PIPP-R has been tested for reliability, construct validity and clinical utility, all with results indicating good psychometrics [50]. The PIPP-R evaluates three behavioral facial actions (brow bulge, eye squeeze and nasolabial furrow), two physiological items (heart rate, oxygen saturation), and two contextual items (gestational age and behavioral state). The PIPP-R gives a weighted and higher score for the youngest infants to adjust for their lesser ability to show signs of pain. Scores can range from 0 to 21 where a higher score signifies a higher level of rated pain. A PIPP-R pain assessment includes a 15 s baseline measurement of heart rate and oxygen saturation together with an observation of the infant’s behavioral state and gestational age. Changes in physiological and behavioral indicators from baseline are then assessed during the first 30 s of the painful procedure. PIPP-R scores will be assessed from video recordings after the procedure by a trained nurse and a subset will also be assessed by one of the researchers for interrater reliability [50].

Galvanic skin response (GSR) refers to changes in sweat gland activity in response to a sensory stimulus. GSR measurements detects changes in electrical (ionic) activity resulting from changes in sweat gland activity. The increase in skin conductance reflects the infant’s arousal intensity in response to the sensory stimulus. As an indicator of pain, skin conductance measurements have detected increased sweating in newborn infants < 28 + 0 postnatal age submitted to heel lancing [53]. GSR have been tested in several neonatal pain studies on term and preterm infants, measuring skin conductance that reflects pain-related activation of the sympathetic nervous system [52–55]. Analyses of GSR are presented with the following variables; area small peaks, area huge peaks (both representing forcefulness of sympathetic nerve firing), peaks per second (the rate of firing in the sympathetic nerves), average rise time, average peak. Higher values in any of the above GSR parameters are indicative of more stress [52].

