## Methods: data collection, data analyses and management, data monitoring

### Data collection

Demographic data of the parent-infant dyad is registered before the procedure starts, including registration of potential music and singing activities during pregnancy for the parents in group 3. In all groups: before, during and after the procedure the infant will have a saturation probe attached to one foot making it possible to measure heart rate and oxygen saturation and electrodes measuring galvanic skin response on the other foot. The infant’s face and pulse oximetry values will be videotaped for later pain assessment with PIPP-R. An experienced midwife/nurse will perform the venipuncture. Venipuncture is routinely used in all hospitals in Swedish neonatal and postnatal care since it is considered less painful for the infant than heel lance [56]. A tourniquet using a soft cotton band is applied, the skin is disinfected, and a 21–23 Gauge needle is used for the blood sampling. The infant will be monitored until the treatment is concluded. In case of failed attempts, only the first venipuncture will be used in the study. In the breastfeeding condition, the midwife/nurse will make sure that the infant is latched and sucking well before the blood test is performed to safeguard the analgesic effect of breastfeeding. The infants’ behavioral responses to pain together with oxygen saturation and heart rate values are videotaped with two digital video cameras and will be assessed subsequently from the video films.

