### Data analyses, management and monitoring

Methods for statistical analyses are chosen depending on scales of measurement and normal distribution. The data will be analyzed with descriptive and comparative statistics. Continuous variables that are normally distribute will be presented with mean and standard deviation and compared with t-test for two groups and ANOVA for multiple groups. For data that doesn’t fulfil those criteria we will use median with interquartile range and Mann-Whitney U-test or Kruskall-Wallis one way analysis of variance, respectively. Intention-to-treat will be used, including all randomized parent-infant dyads in the analysis. The division of group 2 into 2a and 2b, which is a nomenclature to distinguish breastfeeding from no breastfeeding, will be taken into account in the comparative analyses and differences between the two subgroups will be scrutinized. Cohens kappa will be used to calculate interrater reliability between PIPP-R scorers.

The data collected in the study is safely stored on a secure server at Örebro University. The project folder on the server is only available to the researchers in the project and is automatically backed-up. The principal investigator is responsible for the data monitoring, ensuring that the researchers in the study are carrying out the research according to the research protocol, ensuring intervention fidelity in the live parental lullaby singing via recurring spot checks with microanalysis of the live singing, ensuring the research is keeping to time and budget and that the research is being conducted ethically. The research group will meet regularly to ensure consistency. During the original development of the project proposal of the SWEpap-study, the research group consulted with parents with previous extensive experience of NICU care. These parents will continue to give feedback on demand.

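### The GSR outcome is a change with no stated reference time, compared without baseline adjustment; a baseline taken before treatment and used as a covariate would be more precise and would remove a possible contamination

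*Protocol article*

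**What the plan says.** All references are to the Protocol article.

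- **Outcomes** lists as the first secondary outcome "changes in galvanic skin response (GSR) (area small peaks, area huge peaks, peaks per second, average rise time, average peak". No reference time is given.
- **Study measures** explains that "Galvanic skin response (GSR) refers to changes in sweat gland activity in response to a sensory stimulus" and then says "Analyses of GSR are presented with the following variables; area small peaks, area huge peaks", followed by the remaining parameters. Higher values of any of them are read as more stress. The only baseline defined there belongs to PIPP-R: "a 15 s baseline measurement of heart rate and oxygen saturation". None is defined for GSR.
- **Data collection** states for all groups that "before, during and after the procedure the infant will have a saturation probe attached to one foot", with "electrodes measuring galvanic skin response on the other foot". When the electrodes go on relative to the start of treatment is not said.
- **Table 1** (under Eligibility criteria) places the infant in the skin-to-skin arms on the parent's "bare chest 10 min before the venipuncture". Humming in group 3 starts at that same moment. Breastfeeding and glucose start about 2 min before.
- **Data analyses, management and monitoring** says that normally distributed continuous variables are "compared with t-test for two groups and ANOVA for multiple groups", and otherwise by Mann-Whitney or Kruskal-Wallis. Neither branch names a baseline covariate.

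**The concern.** There are two separate issues.

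**Precision.** A pre-procedure GSR value is recorded, but the stated comparison does not use it as a covariate. Whether the quantity tested is a difference from baseline or the level during puncture, an unadjusted test gives wider intervals than one adjusted for an untreated baseline.

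**Meaning of the change.** Treatment is already running before the needle. If the reference window lies inside that period, an arm whose infants are already calmer starts from a lower value. Subtracting that value removes part of the benefit that the trial wants to measure. The stretch under treatment also differs by arm, so the same clock time before the needle does not mean the same thing in each group.

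At stake is how sharply one instrumental secondary outcome can be read, and how it should be interpreted. The PIPP-R comparison does not depend on it.

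**Working it through.** The article gives no effect size, SD, correlation or power for GSR (its sample size section concerns PIPP-R only), so there is no GSR figure to reproduce.

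**Step 1. What each possible reference window would contain (treatment starts from Table 1)**

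| Window before needle | Group 1 | Group 2 | Group 3 |
|---|---|---|---|
| Earlier than 10 min | no treatment with a stated start | none | none |
| 10 to 2 min | no treatment with a stated start | skin-to-skin | skin-to-skin, humming |
| Last 2 min | glucose | skin-to-skin, with breastfeeding in 2b | skin-to-skin, humming, breastfeeding if applicable |

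Only the first window is free of timed treatment in every arm. The middle one is treated in groups 2 and 3 but precedes glucose in group 1. In the last one all arms are treated, in different ways.

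**Step 2. Precision with an untreated baseline**

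Take equal SD before and during puncture, and let r be the correlation between the two. In units of the single-measurement variance:

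- change score: 2(1 − r)
- level during puncture, unadjusted: 1
- ANCOVA on baseline: 1 − r²

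The ratio of change score to ANCOVA is 2(1 − r)/(1 − r²) = 2/(1 + r).

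| r (assumed) | Change | ANCOVA | Change/ANCOVA | ANCOVA n per group matching 75 analysed as change |
|---|---|---|---|---|
| 0.3 | 1.40 | 0.91 | 1.54 | 75 × 0.65 ≈ 49 |
| 0.5 | 1.00 | 0.75 | 1.33 | 75 × 0.75 ≈ 56 |
| 0.7 | 0.60 | 0.51 | 1.18 | 75 × 0.85 ≈ 64 |
| 0.9 | 0.20 | 0.19 | 1.05 | 75 × 0.95 ≈ 71 |

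For an assumed effect of 0.5 SD with 75 per group, power (change against ANCOVA) is 0.74 against 0.89 at r = 0.3, 0.87 against 0.94 at r = 0.5, and 0.98 against 0.99 at r = 0.7.

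If the outcome is really the level, the unadjusted test has 1/(1 − r²) times the ANCOVA variance: 1/0.91 = 1.10 at r = 0.3 and 1/0.75 = 1.33 at r = 0.5. ANCOVA is thus at least as precise under either reading.

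The direction does not need equal SDs. With SDs s_b (baseline) and s_y (puncture), change variance minus ANCOVA variance is s_b² + s_y² − 2r·s_b·s_y − s_y²(1 − r²) = (s_b − r·s_y)², which is never negative.

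**Step 3. If the baseline is already treated**

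Let f be the share of the between-arm difference at the needle that is already present at baseline. The change score recovers 1 − f of that difference. ANCOVA on the same treated baseline recovers 1 − r·f. At f = 0.5 (assumed), the change score recovers 50%, and ANCOVA 85%, 75% and 65% at r = 0.3, 0.5 and 0.7. A simulation at f = 0.5, r = 0.5 and a true difference of −0.50 gave −0.251 for change and −0.376 for ANCOVA, as the formulas predict (−0.25 and −0.375).

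Adjusting for a treated baseline is therefore not a cure. The baseline has to come before treatment.

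**The case against.** The strongest reply is that the article fixes neither a change score nor a GSR baseline.

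- The word for change in Outcomes may only echo the definition of GSR in Study measures, where level-type parameters follow. That is fair. It removes the certainty that a post-minus-pre score is meant, but not the precision argument, which holds for levels too.
- A reader might infer that the GSR comparison is biased against the parent-driven arms. The documents do not support this. No window is stated, and electrodes may already go on before treatment. Group 1 receives glucose before the needle as well, so only a net difference between arms would matter, and neither its size nor its direction is given. If reactivity to the needle is the target, a change from the pre-needle level is a different estimand rather than a biased one.
- The variance ratios are least-squares results and do not carry over exactly to the rank tests, which may well apply to GSR areas and peaks. This stands.
- Windows and covariates for a secondary outcome are often left to a fuller protocol or analysis plan. This stands in part. However, the article does state its comparison tests, and they are unadjusted. Electrode timing is also a matter of data collection: if no untreated stretch is recorded, no later analysis plan can supply one.
- It would overstate GSR to call it the main objective outcome. It is one of four secondary outcomes. Choosing one lead parameter among the five is optional and is not part of this point.

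**Conclusion.** The point holds as a minor improvement to a secondary outcome. The change in GSR has no reference time, and the stated tests leave out a pre-procedure value that is recorded. With an untreated baseline and equal variances, a change score carries 54% more variance than ANCOVA at r = 0.3, 33% more at r = 0.5 and 5% more at r = 0.9. The correlation is an assumption throughout, and the gain is small if it is high. Contamination of the baseline by treatment is a possibility created by the 10 min and 2 min treatment starts. It is not shown, and its size cannot be derived from the article. The primary conclusion on PIPP-R is unaffected.

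**What to change.** 1. State the GSR reference window, and place it in all arms before any allocated treatment begins.
2. State the GSR window during puncture, and compare the level in that window between arms by ANCOVA, with the pre-treatment value as covariate. If the distribution is not normal, use a transformed or rank-based version. This replaces an unadjusted test of change or level.
3. If reactivity from the pre-needle level is also of interest, report it separately and label it as a different quantity.

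The cost is that electrodes go on a few minutes earlier, the recording is slightly longer, and the analysis wording changes. If electrodes are already attached before treatment, only the wording changes. No additional infants are needed.

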### Study measures

The PIPP-R has been tested for reliability, construct validity and clinical utility, all with results indicating good psychometrics [50]. The PIPP-R evaluates three behavioral facial actions (brow bulge, eye squeeze and nasolabial furrow), two physiological items (heart rate, oxygen saturation), and two contextual items (gestational age and behavioral state). The PIPP-R gives a weighted and higher score for the youngest infants to adjust for their lesser ability to show signs of pain. Scores can range from 0 to 21 where a higher score signifies a higher level of rated pain. A PIPP-R pain assessment includes a 15 s baseline measurement of heart rate and oxygen saturation together with an observation of the infant’s behavioral state and gestational age. Changes in physiological and behavioral indicators from baseline are then assessed during the first 30 s of the painful procedure. PIPP-R scores will be assessed from video recordings after the procedure by a trained nurse and a subset will also be assessed by one of the researchers for interrater reliability [50].

Galvanic skin response (GSR) refers to changes in sweat gland activity in response to a sensory stimulus. GSR measurements detects changes in electrical (ionic) activity resulting from changes in sweat gland activity. The increase in skin conductance reflects the infant’s arousal intensity in response to the sensory stimulus. As an indicator of pain, skin conductance measurements have detected increased sweating in newborn infants < 28 + 0 postnatal age submitted to heel lancing [53]. GSR have been tested in several neonatal pain studies on term and preterm infants, measuring skin conductance that reflects pain-related activation of the sympathetic nervous system [52–55]. Analyses of GSR are presented with the following variables; area small peaks, area huge peaks (both representing forcefulness of sympathetic nerve firing), peaks per second (the rate of firing in the sympathetic nerves), average rise time, average peak. Higher values in any of the above GSR parameters are indicative of more stress [52].

For the parents’ ratings, a visual analogue scale (VAS) with a 10-cm line anchored at the ends is used; from “no pain” on the left end point, up to “worst imaginable pain” on the right end point, from “no stress” on the left end point, up to “worst imaginable stress” on the right end point and finally from “not beneficial” on the left end point, up to “most beneficial possible” on the right end point of the VAS scale. The parents will perform the rating on the VAS scales right after the blood sampling procedure.

### Sample size

No previous RCT has examined the effects of parent-driven pain management in newborn infants by combining SSC, breastfeeding and live parental lullaby singing. Based on previous studies using PIPP-R or its predecessor PIPP in pain alleviation projects, a difference of two PIPP-R points between standard care (group 1) and the full parent driven pain management (group 3) is considered clinically important. Based on those studies we also assume a standard deviation around 2 points. A power calculation sets the number of infants to include in the study to 63 in each group, with a power of 0.8 and a significance level set to 0.05 (www.clincalc.com). To compensate for possible dropouts, incomplete data, such as equipment malfunction or blood sample collection failure, 75 infants per group will be enrolled, making a total of 225 infants.

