### Study design

This is a multi-center, randomized controlled trial (RCT) with three parallel groups with the allocation ratio 1:1:1.

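### The 63 infants per group do not follow from the stated inputs: 2 points with SD 2 needs 16 to 17 per group, and 63 would give power above 0.999 rather than 0.8

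*Protocol article*

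**What the plan says.** The Study design section describes "three parallel groups with the allocation ratio 1:1:1". The Sample size section of the protocol article then gives a complete calculation:

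- **Comparison and difference:** "a difference of two PIPP-R points between standard care (group 1) and the full parent driven pain management (group 3) is considered clinically important".
- **Variability:** "we also assume a standard deviation around 2 points".
- **Error rates:** "with a power of 0.8 and a significance level set to 0.05". Whether the test is one- or two-sided is not stated.
- **Result:** "A power calculation sets the number of infants to include in the study to 63 in each group, with a power of 0.8".

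An allowance for dropout and incomplete data is added after this step. It raises 63 to 75 per group, 225 in total. The section mentions no multiplicity correction, no inflation for clustering by hospital, and no other comparison or smaller difference as the basis for 63. The section Data analyses, management and monitoring names the t-test for two groups and ANOVA for several, with rank-based tests if the data are not normal.

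**The concern.** The stated difference equals the stated SD, so the standardised effect is 1.0. An effect that large needs fewer than 20 per group at conventional error rates, and 63 is nearly four times that.

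This is the only sample-size statement in the article and its only justification for enrolling 225 newborns. As printed, a reader cannot tell what effect the trial was sized for. The two simplest explanations have different consequences:

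- **If the SD used was 4,** the printed variability is too small by a factor of two. Anyone who reuses SD 2 to plan a later trial for the same difference would arrive at about a quarter of the infants needed (16 against 63).
- **If the target was 1 point,** the trial was sized for half the difference that the article calls clinically important.

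If instead 2 points and SD 2 are both right, the power is not 0.8 but close to 1, and differences well below 2 points will usually be statistically significant.

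**Working it through.** **Inputs** (Sample size section unless noted): difference Δ = 2; SD σ = 2; power 0.8; α = 0.05, taken as two-sided because the article does not say; equal allocation (Study design); two-sample t-test for groups 1 and 3 (Data analyses, management and monitoring).

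**1. Attempt to reproduce the stated figure.** With d = Δ/σ = 2/2 = 1.0,

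n per group = 2 × ((1.960 + 0.842)/d)² = 2 × (2.802/1.0)² = 15.7, so 16.

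The exact t-test gives 16.7, so 17. The stated 63 is not reproduced: it is 63/17 = 3.7 to 63/16 = 3.9 times the required number.

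**2. Power of 63 on the stated inputs.** The standard error of the difference is 2 × √(2/63) = 0.356. Then 2/0.356 = 5.61, and 5.61 − 1.96 = 3.65, which gives power 0.9999 by the normal formula and 0.9998 by the t-test. With 75 per group the t-test power is 0.99998.

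**3. What does give 63.** With d = 0.5, n = 2 × (2.802/0.5)² = 62.8, so 63. The t-test gives 63.8, so 64, and at 63 its power is 0.795. An effect of 0.5 corresponds to 1 point at SD 2, or 2 points at SD 4.

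**4. Other readings of the calculation, with Δ = 2 and σ = 2.**

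| Variant | n per group, normal formula | n per group, t-test |
|---|---|---|
| One-sided 0.05 | 13 | – |
| α/3 (three pairwise tests) | 21 | 23 |
| α/6 | 25 | 27 |
| α/3 with power 0.95 | 33 | 35 |
| α = 0.001 with power 0.95 | 49 | 52 |

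A three-group ANOVA with a 2-point range of means needs about 16 to 21 per group. Mann-Whitney at its lowest relative efficiency, 0.864, needs 17/0.864 = 19.7, about 20. None of these gives 63.

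**5. Does the looseness of the stated SD explain it?** For a 2-point difference:

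| SD | n per group (normal formula) | Power at 63 (t-test) |
|---|---|---|
| 2.0 | 16 | 0.9998 |
| 2.5 | 25 | 0.994 |
| 3.0 | 36 | 0.960 |
| 3.5 | 49 | 0.889 |
| 4.0 | 63 | 0.795 |

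Power of 0.8 for 2 points at 63 per group requires an SD of about 4 (3.98 by the t-test). With 75 per group the limit is 4.34.

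**6. Smallest difference with 80% power if SD 2 is right:** 1.01 points at 63 per group and 0.92 at 75, about half of the stated 2 points.

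**The case against.** Four points can be made in the plan's defence.

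- **The stated power need not be the wrong figure.** If the calculator was given SD 4, or a 1-point difference, then 63 and 0.8 are both right and another input is misreported. This stands. The article shows that the four figures conflict, not which one is in error. The power above 0.999 holds only if 2 points and SD 2 are both correct.
- **The consequence is mild.** On the stated inputs the trial is too large, not too small, and at SD 4 it is adequate. The infants have the routine screening test in any case, and every group receives pain management, so extra enrolment adds no needle procedures. The error does not bias the estimate or change the analysis. All of this stands. It limits the harm but does not make the statement correct.
- **An unstated refinement could explain 63.** Multiplicity does not: α/3 gives 21 to 23. Dropout does not, because it is added afterwards. Reading 63 as a total (3 × 21) fails, because the text says that it applies to each group and 75 × 3 = 225 builds on that.
- **The article condenses a fuller protocol.** That would excuse an omission. Here every input and the result are printed, and they disagree.

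**Conclusion.** The concern holds. With a 2-point difference, SD 2, two-sided α of 0.05 and power 0.8, the requirement is 16 to 17 per group, not 63. At 63 per group those inputs give power of about 0.9998, not 0.8. No variant of the test, the significance level or the power that was tried restores agreement, and the SD would have to be about 4 rather than around 2. The conclusion rests only on figures printed in the article plus the two-sided convention; a one-sided test would widen the gap (13 per group).

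Which figure is wrong cannot be settled from the article. The most likely source is a standardised effect of 0.5. The trial's ability to compare groups 1 and 3 is not in doubt up to an SD of about 4. What fails is the justification of the size, which must be corrected because it is wrong as written.

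**What to change.** The sponsor should recover the inputs actually given to the calculator and restate the paragraph so that the difference, SD, power and size agree. Depending on what was intended, it should say one of the following:

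- 63 per group gives 80% power for a 1-point difference at SD 2. In that case, also explain why 1 point is the planning target when 2 points is called clinically important.
- 63 per group gives 80% power for a 2-point difference at SD 4. In that case, correct the SD and its basis in the earlier studies.
- At 2 points and SD 2, the power with 63 per group exceeds 99.9%. In that case, give the reason for enrolling more than the 16 to 17 per group that the inputs require.

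The paragraph should also say that the test is two-sided, if it is. The cost is the rewording of one paragraph. Enrolment of 75 per group and the analysis stay as they are.
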